**Figure 5 clc70353-fig-0005:**
[figure not shown]
“Treatment assessment algorithm” integrated into the electronic case report form to determine the use or non‐use of guideline‐directed medical therapies by registry participants. Step‐1: Determine the evidence‐based medication classes* (RAS inhibitors, β‐blockers, MRAs, and SGLT‐2 inhibitors) used by the registry participants. Step‐2: In instances where patients were not receiving treatment for HF, the patient and participant physician were asked to provide a rationale** (e.g., symptomatic hypotension for RAS inhibitors, bradycardia for β‐blockers, hyperkalemia for MRAs, or urinary tract infections for SGLT‐2 inhibitors). Step‐3: In instances where patients were receiving treatment for HF, determine the molecule that the participant used*** (e.g., ramipril for RAS inhibitors, bisoprolol for β‐blockers, eplerenone for MRAs, and dapagliflozin for SGTL‐2 inhibitors). Step‐4: Determine the daily dosage of medication that the participant used (e.g., ramipril 2.5 mg once daily, bisoprolol 10 mg once daily, eplerenone 25 mg once daily, and dapagliflozin 10 mg once daily). Step‐5: Determine whether the participant used the target dose of treatment or not# (< 50% of target dose, ≥ 50% to < 100% of target dose, or ≥ 100% of target dose).

#### Additional Clinical Data Collection for Hospitalized Patients With Acute HF

2.5.9

The study timeline for clinical data collection from hospitalized patients with acute HF is presented in the figure. Initially, the participating physicians ascertained the clinical manifestations of acute HF, including acute decompensated HF, acute pulmonary edema, cardiogenic shock, and isolated right ventricular failure [2]. In addition to the sociodemographic and clinical data previously referenced, management strategies will be documented for hospitalized patients diagnosed with acute HF. In‐hospital management strategies encompass oxygen therapy, ventilatory support (noninvasive and/or invasive mechanical ventilation), intravenous treatments (diuretics, inotropes, and/or vasopressors), device therapies (pacemaker, implantable cardioverter‐defibrillator, and cardiac resynchronization therapy), renal replacement therapy, invasive procedures (percutaneous coronary intervention, transcatheter aortic valve replacement, mitral or tricuspid valve transcatheter edge‐to‐edge repair), and mechanical circulatory support devices (intra‐aortic balloon pump, extracorporeal membrane oxygenation, or ventricular assist device therapies) will be registered (Figure 6).

**Figure 6 clc70353-fig-0006:**
[figure not shown]
Data elements and time points for hospitalized patients with acute heart failure.

In‐hospital complications, including acute myocardial infarction, cardiogenic shock, ischemic stroke, transient ischemic attack, systemic embolism, deep venous thrombosis, acute pulmonary embolism, atrial and ventricular arrhythmias, second‐ or third‐degree atrioventricular block, acute renal failure, major bleeding, and sepsis, will be documented. During the hospitalization period, if it occurs, the cause of cardiovascular death (WHF, acute myocardial infarction, sudden cardiac death, arrhythmia, stroke, or others) or non‐cardiovascular death (malignancy, systemic infection and sepsis, respiratory failure, renal failure, and others) will also be documented (Figure 6).

A comprehensive evaluation of the patient will be conducted at the time of hospital (or emergency department) admission and again before discharge, encompassing a physical examination, electrocardiographic and echocardiographic data, and laboratory results. We aimed to assess the effects of in‐hospital management strategies on clinical status, physical examination, electrocardiographic, echocardiographic, and laboratory variables. Similarly, we will assess the use of evidence‐based oral HF therapies, including RAS inhibitors, β‐blockers, MRAs, and SGLT‐2 inhibitors, before, during, and after hospitalization. This assessment aimed to determine the in‐hospital optimization of GDMT and its prognostic effectiveness in registry participants (Figure 6).

### Follow‐Up Visits

2.6

Longitudinal data will be collected at regular outpatient visits every 6 months, with a margin of error of 1 month, or via telephone interviews if the patient is not eligible for outpatient visits (Figure 2). During follow‐up visits, physical examination findings, electrocardiographic and echocardiographic data, laboratory results, and a comprehensive assessment of HF therapies will be obtained. Follow‐up information will be obtained for clinical outcomes (hospitalization for HF and survival) and changes in HF medications. Participants enrolled in the TURK‐HF registry will undergo frailty assessment and, if available, complete the EQ‐5D‐5L questionnaire to determine longitudinal changes in frailty status and HRQoL during follow‐up visits.

### Clinical Endpoints

2.7

The clinical endpoints of the TURK‐HF registry will reflect clinical “hard” endpoints, including cardiovascular mortality or all‐cause mortality, morbidity outcomes (HF‐related hospitalizations or unplanned emergency department visits requiring intravenous diuretic therapy), clinician‐interpreted outcomes (e.g., NYHA functional class), patient‐reported outcomes (e.g., HRQoL), and surrogate endpoints (e.g., N‐terminal pro‐brain natriuretic peptide levels), either alone or in combination.

The utilization of composite clinical endpoints is a prevalent practice in clinical trials. The time‐to‐first‐event method is the most common approach for analyzing composite endpoints. However, this method is subject to an inherent limitation in that it treats all contributory endpoints equally in terms of their severity. There is growing recognition of the importance of hierarchical composite clinical outcomes and “the win ratio” in cardiology trials [32]. Win ratio analysis prioritizes the most clinically significant component of the composite endpoints by assigning a greater ranking weight to the constituent component [33]. Thus, we will use the win ratio method to analyze the composite outcomes of the TURK‐HF registry.

We will also obtain follow‐up data on classical 3‐point major adverse cardiovascular events, including nonfatal stroke, nonfatal myocardial infarction, and cardiovascular death. Clinical data on hospitalization due to atrial or ventricular arrhythmias, hospitalization due to non‐cardiovascular causes, and left ventricular assist device implantation will be recorded.

### Current Situation

2.8

The first participant was enrolled in the TURK‐HF registry on January 8, 2025. To date, we have registered 1240 patients with HF within the first 6 months of the study. The initial baseline results of the TURK‐HF registry will be announced after a 1‐year enrollment period. Subsequently, we intend to publish several scientific papers addressing the gaps and potential questions within the HF population.

## Discussion

3

The TURK‐HF registry will be the first national, large‐scale, multicenter, prospective, and observational study comprising outpatients and hospitalized patients with HF, irrespective of their LVEF, conducted in Türkiye. The primary goal of the present registry is to determine the epidemiology, sociodemographic and clinical characteristics, diagnostic approaches, management strategies, and long‐term prognosis of patients with HF in a real‐world setting. The six fundamental research questions that the TURK‐HF registry aimed to answer are as follows: (i) the impact of SES on the utilization of GDMT and prognosis in patients with HF; (ii) the temporal changes in frailty and HRQoL and its association with subsequent prognosis; (iii) diagnostic approaches, algorithms, and scoring systems for patients with HFpEF; (iv) the comorbidity burden in patients with HFpEF and the phenotypes of HFpEF; (v) the patient, physician, and healthcare system‐related barriers for the suboptimal use of evidence‐based therapies, its prognostic impact, and the strategies to improve the implementation of GDMT; and (vi) in‐hospital management strategies, complications, and prognosis in patients with acute HF.

Previous studies conducted in Western countries have demonstrated that patients with low SES have a higher incidence and prevalence of HF [34, 35]. A published post hoc analysis of the study reported worse clinical outcomes in patients with lower SES [36]. However, the socioeconomic structure of Türkiye differs from that of European, American, and Far Eastern countries, and national data from Türkiye on the impact of SES on the use of GDMT and prognosis in patients with HF are lacking. Therefore, the collection of current data from the real‐life registry is crucial to understand the actual relationship between SES and access to healthcare, receiving GDMT, and prognosis in patients with HF in Türkiye. For the first time, the TURK‐HF registry used the analytic approach described by Boratav to determine the SES of the study participants [16]. As Boratav posits, social classes and individuals' SES are delineated by their relationships within the production process, which are predicated on the control over the means of production. Thus, the TURK‐HF registry design will allow us to obtain detailed data on the participants' control over the means of production, in addition to classical SES variables, including marital status, living area, and education level.

The diagnosis of HFpEF presents challenges due to its multifactorial etiologies and the lack of a definitive diagnostic test. The H_2_FPEF score was created to aid in diagnosing HFpEF. It originated from a study involving 414 patients in the United States with an LVEF of 50% or higher, where the HFpEF diagnosis was confirmed through invasive hemodynamic stress testing [29]. Nonetheless, there is conflicting data concerning the use of scoring systems and their diagnostic utility within the Turkish population. To address this, for the first time, we incorporated an automatic calculation system into the TURK‐HF registry as a “decision support tool” to compute the H_2_FPEF score for patients with HFpEF. This unique approach will provide comprehensive data on the use and diagnostic power of the present scoring system in real‐world patients with HF.

It is widely recognized that patients with HFpEF constitute a heterogeneous cohort, and a “one size fits all” management strategy for HFpEF is inappropriate for this patient population. The clustering strategy to identify distinct phenogroups within populations of patients with HFpEF provides data for patient‐level treatment according to comorbidities and risk factors [37, 38]. A prospective study conducted in the United States identified distinct characteristics among three phenogroups. Phenogroup 1 consisted of younger individuals with lower levels of BNP. Phenogroup 2 demonstrated the highest prevalence of obesity, diabetes mellitus, and obstructive sleep apnea. Conversely, phenogroup 3 comprised the oldest individuals, who were most likely to have chronic kidney disease and exhibited the highest BNP levels [37]. Similarly, a study of the TOPCAT trial participants revealed that phenogroup 1 patients were younger, had a higher prevalence of smoking, and had preserved functional class; phenogroup 2 patients were older with left atrial enlargement and a higher prevalence of atrial fibrillation; and phenogroup 3 patients demonstrated more functional impairment, obesity, diabetes, chronic kidney disease, and concentric LV hypertrophy [38]. To date, clustering strategies and phenogroups within the Turkish population affected by HFpEF have not been studied. The TURK‐HF registry will provide the first national real‐world data on the phenotypes of patients with HFpEF in Türkiye. This initiative will enable personalized treatment strategies for these heterogeneous groups in the era of precision medicine.

Suboptimal implementation of evidence‐based HF treatment, particularly in HFrEF, has been documented in various registries [4, 5, 6, 39, 40]. While most reports have been predominantly descriptive, detailing the percentage usage of fundamental HF medications, they often lack comprehensive information on diagnostic methodologies and additional pertinent medications, devices, and interventions. Well‐structured registries have the potential to collect extensive descriptive data and analyze and quantify the underlying causes of inadequate implementation. This can facilitate the identification of specific patient groups with the most significant unmet needs or areas requiring improvement, thereby enabling targeted initiatives to enhance the implementation. The TURK‐HF registry will provide detailed real‐world data on the management strategies used for patients with HF. For this purpose, we created a unique algorithm and integrated it into the e‐CRF as a “work‐up tool” for the first time in Türkiye. This approach included five consecutive questions about the use or non‐use of GDMT in HF. As outlined in the methods section, we questioned the use of treatment classes and scrutinized the specific molecule prescribed and its daily dosage for each category of evidence‐based HF medication. In this way, we will assess the use or nonuse of the target dose or the maximally tolerated dose of HF medications in patients with HF. Furthermore, we examined the justification for the absence of GDMT utilization, considering factors such as contraindications, intolerability, and clinical inertia. Analyzing the real‐world factors and obstacles hindering the effective implementation of GDMT through the TURK‐HF registry offers a unique opportunity to address these challenges in Türkiye.

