### Study Sites and Participant Physicians

2.2

The TURK‐HF registry will be conducted in seven distinct geographical regions in Türkiye. The study sites were identified according to the Nomenclature of Territorial Units for Statistics (NUTS) Level 1 classification system to reflect the population distribution of geographical regions [13]. Detailed data on the cities, NUTS regions, and study sites are presented in Table 1 and Figure 1. To reflect the characteristics of health providers, the study sites were selected based on the projected distribution of health provider subgroups, as presented in the Health Statistics Yearbook [14]. The participant physicians were offered participation by the project coordinator. It was made clear that participation was voluntary and that no financial compensation would be provided for participation. A total of 46 investigators from 38 centers (16 university hospitals, 13 education and research hospitals or city hospitals, 4 state hospitals, and 5 private hospitals) in 22 cities across Türkiye participated in the study (Table 1 and Figure 1). The diagnosis of HF, initiation, up‐titration, and maintenance of HF treatments, disease management, and treatment‐related adverse events and complications are beyond the scope of this registry and are the responsibility of the participating physicians.

**Table 1 clc70353-tbl-0001:** Nomenclature of Territorial Units for Statistics (NUTS) Level 1 regions, cities, and study sites of the TURK‐HF registry.

NUTS Level 1 region	City	Study site
Aegean (TR3)	Izmir	Baskent University, Faculty of Medicine, Department of Cardiology
	Izmir	Medicana International Izmir Hospital, Department of Cardiology
	Izmir	Izmir University of Economics, Faculty of Medicine, Department of Cardiology
	Izmir	Ege University, Faculty of Medicine, Department of Public Health
	Kütahya	Kutahya Health Sciences University, Faculty of Medicine, Department of Cardiology
	Manisa	Manisa Celal Bayar University, Department of Cardiology, Manisa
	Manisa	Manisa City Hospital, Department of Cardiology, Manisa
	Manisa	Akhisar Mustafa Kirazoglu State Hospital, Department of Cardiology, Manisa
	Denizli	Pamukkale University, Department of Cardiology, Denizli
Istanbul (TR1)	Istanbul	Istanbul University‐Cerrahpasa Institute of Cardiology, Department of Cardiology
	Istanbul	Bakirkoy [name] Training and Research Hospital, Department of Cardiology
	Istanbul	[name] Training and Research Hospital, Department of Cardiology

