### Study Population

2.3

The only inclusion criterion for the TURK‐HF registry was the presence of HF as determined by the participating physician. The exclusion criteria were age < 18 years and refusal to provide informed consent for registry participation. All patients will be eligible for enrollment, regardless of LVEF (HFrEF, HFmrEF, or HFpEF) or whether they have de novo or chronic HF. All patients will be enrolled in the study, regardless of their clinical status. This encompasses both those presenting for a non‐urgent outpatient visit with stable signs and symptoms and those requiring urgent care for WHF. The objective of this approach was to ensure the representativeness of the study population to the source population to generalize the aim of generalizability of data and externally validate the registry data. WHF is defined as worsening symptoms and signs of HF in patients with chronic HF, requiring hospitalization and/or intravenous diuretic therapy [11]. All study participants provided written informed consent.

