### Baseline Clinical Assessment of Patients

2.5

The baseline assessment of patients will include sociodemographic data, primary care access information, frailty assessment, health‐related quality of life (HRQoL) questionnaire, HF‐related information, medical history and comorbidities, physical examination findings, electrocardiographic and echocardiographic data, H_2_FPEF score calculation for patients with HFpEF, laboratory results, and medical and device‐based HF therapies (Figure 2).

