#### H_2_FPEF Score Calculation

2.5.7

It is critical that scoring systems accurately determine the probability of HFpEF to enable clinicians to decide whether HFpEF is present. The validated H_2_FPEF score utilizes six clinical and echocardiographic parameters to accurately distinguish HFpEF from the non‐cardiac causes of dyspnea [29]. A meta‐analysis reported that a high H_2_FPEF score is associated with an increased risk of HF‐related hospitalization and all‐cause mortality in patients with dyspnea and normal LVEF [30]. However, there are conflicting data regarding the use of scoring systems and their diagnostic utility in the Turkish population [31]. Therefore, we integrated an automatic calculation system into the e‐CRF as a “decision support tool” to calculate the H_2_FPEF score in patients with HFpEF (Figure 4).

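### The registry promises the diagnostic power of the H2FPEF score, but it enrols no non-cases and describes no independent reference diagnosis, so diagnostic accuracy cannot be estimated

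*Protocol article*

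**What the plan says.** Section 2.5.7 presents the H2FPEF score as a means of telling HFpEF apart from non-cardiac breathlessness. It notes conflicting evidence on such scores in the Turkish population and says that an automatic calculator was therefore placed in the e-CRF, as a decision support tool, "to calculate the H_2_FPEF score in patients with HFpEF". The baseline list in section 2.5 has the same restriction: "score calculation for patients with HFpEF". The Discussion repeats the point about conflicting Turkish data, offers the calculator as the response, and concludes: "This unique approach will provide comprehensive data on the use and diagnostic power of the present scoring system in real‐world patients with HF".

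On who enters the registry, section 2.3 states: "The only inclusion criterion for the TURK‐HF registry was the presence of HF as determined by the participating physician". On who makes the diagnosis, section 2.2 lists the diagnosis of heart failure among the matters that "are beyond the scope of this registry and are the responsibility of the participating physicians". For the study in which the score was derived, the Discussion says that HFpEF was confirmed by invasive hemodynamic stress testing. The article describes no comparable standard or adjudication for the registry.

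Scoring systems for HFpEF also appear within the third of the six research questions in the Discussion. That question does not mention accuracy.

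**The concern.** Diagnostic power means how well a score separates patients who have the condition from those who might have it but do not. Measuring it needs both kinds of patient and a reference diagnosis that does not depend on the score. The registry, as described, has only the first kind, labelled by the physician who also enters the data.

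What is at stake is a conclusion. The article links the calculator to an open national question about the diagnostic usefulness of scoring systems. A later paper reporting the accuracy of the score from these data could be cited as settling that question, although the data cannot address it. Neither a larger sample nor an analysis plan can supply non-cases that were never enrolled, so this is not a detail that a SAP could repair.

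**Working it through.** The article states no sensitivity, specificity, AUC or sample size for this aim, so there is no figure to reproduce. The check is whether each accuracy measure can be estimated at all.

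**Inputs**
- Target contrast: HFpEF against non-cardiac causes of dyspnea (section 2.5.7).
- Entry: physician-determined HF only (section 2.3).
- Patients scored: those with HFpEF (sections 2.5 and 2.5.7, the Figure 4 legend and the Discussion).
- Reference diagnosis: that of the participating physician (section 2.2).
- Enrolled in the first 6 months: 1240 patients with HF (section 2.8). The HFpEF share is not given.

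**The 2×2 table.** Let TP and FN be scored cases with a high and a low score, and FP and TN the same for scored non-cases. Patients with non-cardiac dyspnea do not meet the entry criterion, so FP = TN = 0.

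- Specificity = TN/(TN + FP) = 0/0, undefined.
- Positive likelihood ratio = sensitivity/(1 − specificity), and negative likelihood ratio = (1 − sensitivity)/specificity. Both need specificity, so both are undefined.
- AUC = concordant pairs/(cases × non-cases). The denominator is cases × 0 = 0, so it is undefined.
- Positive predictive value = TP/(TP + FP) = TP/TP = 1 by construction. It carries no information about the score.

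**Dependence on sample size.** Assume HFpEF shares of 20%, 30% and 50% of the 1240 patients, for illustration only:

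| Assumed share | Cases scored | Non-cases scored | Case/non-case pairs |
|---|---|---|---|
| 20% | 248 | 0 | 0 |
| 30% | 372 | 0 | 0 |
| 50% | 620 | 0 | 0 |

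The result is the same in every row, and further enrolment under the same entry rule does not change it.

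**What remains of sensitivity.** TP/(TP + FN) can be computed, but TP + FN is the number of patients whom a physician labelled HFpEF, not the number in whom HFpEF was independently confirmed. The quantity is P(high score | physician label). It equals sensitivity only if the label is correct and was made without the score, and the article establishes neither.

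**Could other enrolled patients serve as non-cases?** The Abstract lists the score without the HFpEF restriction, but sections 2.5 and 2.5.7 and the Discussion apply it. Scoring the other ejection-fraction groups would not help in any case. According to the Discussion, the score was derived in patients with LVEF of 50% or higher. The relevant non-cases are breathless patients in that range without heart failure, and the entry criterion rules them out.

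**The case against.** The strongest reply is that this is one phrase in the Discussion. No endpoint in section 2.7 depends on the accuracy of the score, no accuracy analysis is announced, and the same sentence promises data on use, which the registry can deliver. The third research question can be answered descriptively as worded. All of this stands and limits the severity. It does not rescue the phrase, because the article itself offers the calculator as the response to conflicting diagnostic evidence.

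A reader might go further and infer that physicians see the score before they assign the label, so that the apparent sensitivity is circular and inflated. The documents do not support that as a fact. Visibility is inferred from the term decision support tool, Figure 4 is not available, and the article does not say whether HF type is saved before or after the score appears. If the score is computed only once a patient is recorded as HFpEF, it cannot feed that record. The introduction also separates HFpEF from other heart failure by LVEF, so for an enrolled patient the type follows largely from an echocardiographic measurement. Nor is the direction of bias fixed: with an imperfect label that ignores the score, the share of labelled patients with a high score can fall below the true sensitivity. Influence on the label remains possible, since section 2.5.7 says that such scores help clinicians decide whether HFpEF is present. It is conditional on the display order.

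A reader might also infer that the third research question fails altogether. It does not; only an accuracy reading of it does.

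**Conclusion.** The point holds in a limited form. The Discussion attributes to the registry a property that its design does not have. With zero scored non-cases, specificity, likelihood ratios and AUC cannot be estimated at any sample size. With no reference diagnosis independent of the treating physician, an apparent sensitivity is only the proportion of physician-labelled HFpEF patients with a high score. This rests on the stated entry criterion and the stated restriction of the score, and on no assumed figure. It also takes the article at its word that diagnosis is left to the physician and that no adjudication is planned.

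Influence of the score on the label is a possibility that depends on the e-CRF display order, which the article does not give. No size can be put on it.

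The point should be fixed but does not threaten the registry. The endpoints and the other five research questions are unaffected.

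**What to change.** 1. **Wording.** In the Discussion, replace the promise of diagnostic power with what the registry can give: how the score is used, its distribution among patients with physician-diagnosed HFpEF, and its association with HF hospitalization and death. State that diagnostic accuracy will not be reported, and that the third research question is meant in this descriptive and prognostic sense. The cost is a sentence or two and a weaker claim.

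2. **Display order, if needed.** Establish whether the e-CRF shows the score before HF type is saved. If it does, have HF type saved first for future patients, and flag records entered before the change. The cost is a small programming change and two data-collection regimes, because 1240 patients were already enrolled at the time of writing. Labels already entered cannot be corrected retrospectively. This step protects the label but does not make specificity or AUC estimable. If the label already comes first, no change is needed beyond saying so.

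If diagnostic accuracy is truly wanted, it needs a separate cohort of patients with suspected HFpEF that includes non-cases, with a reference diagnosis made independently of the score. That would be a different study and is not required to correct the article.
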